### Recruitment

We will carry out open recruitment by placing advertisements, and the decision to participate will be made by the subject.

Colored fliers, brochures, and banners will be placed inside of both hospitals. Furthermore, we will place advertisements in the newspaper and on the homepage of the hospitals and the boards of senior welfare centers around the hospitals.

### Randomization

The staff of Hanpoong Pharm & Food Co., Ltd. will first place a numbered label on each YMJ and placebo according to the randomization program results provided by the statistician, and the YMJ and placebo will subsequently be distributed to each clinical center. The randomization result table will remain sealed by the statistician.

After the subject has passed the screening phase, an independent clinical research coordinator (CRC) will control randomization. First, the randomization form containing the basic information of the subject who has passed the screening phase will be transmitted in facsimile to an independent statistician. The randomization number in the randomization form will be left blank before the statistician receives the form. The statistician will make a decision about the randomization number based on the allocation sequence that has been generated by a random number creation program in advance, and the statistician will return the randomization form filled in with the established number (specified ID number) to the CRC. Then, the clinical pharmacist will distribute the corresponding numbered YMJ or placebo to the subject.

The randomization allocation ratio to the sites will be 1:1. The CRC will provide the specified ID number to the investigators. The authorized contract research organization (CRO) will guarantee that all procedures are performed correctly.

### Blinding

The subjects will be blinded to the treatment that they receive. Additionally, the investigator, CRC, and clinical pharmacist will be blinded to the randomization. Only the independent statistician will be involved in the randomization, and the entire procedure will be audited by the authorized CRO (DreamCIS, Seoul, Korea).

### Intervention

#### YMJ

YMJ has long been used in TKM to treat symptoms like dry mouth or throat, emaciation, decreased urine, an irritable rash on the palms and soles, insomnia, and tidal fever caused by ‘*Yin-deficiency*’
[14]. It is composed of six herbs: *Rehmannia glutinosa*, *Cornus officinalis*, *Dioscorea batatas*, *Paeonia suffruticosa*, *Poria cocos*, and *Alisma orientale*[25].

The YMJ that will be used in this trial is a brown, bitter, granular, herbal extract (Hexalong granule®, Hanpoong Pharm & Food Co., Ltd., Jeonju, Korea) produced according to the Korean Good Manufacturing Practice guidelines. Hexalong granule® is permitted and regulated by the Korean Food & Drug Administration. Every 3 g of Hexalong granule (water-extracted YMJ) includes *Rehmannia glutinosa* (2 g), *Cornus officinalis* (1 g), *Dioscorea batatas* (1 g), *Paeonia suffruticosa* (1 g), *Poria cocos* (1 g), and *Alisma orientale* (1 g) as raw materials.

All herbs will be obtained from qualified suppliers in Korea, and water-extracted YMJ granules will be sealed in opaque aluminum bags.

We will administer YMJ to the subjects at a dose of 3 g according to the specialty publication of the standard guidelines of the herbal prescription administration
[26].

#### Placebo

Presently, a standard treatment for xerostomia does not exist. Thus, the placebo YMJ that will be used in this study does not have active components. The placebo YMJ was made with cornstarch powder that has the same color and taste as YMJ by Hanpoong Pharm & Food Co., Ltd. by using their standard method of placebo manufacturing according to the Korean Good Manufacturing Practice guidelines. The placebo YMJ will be packed identically in opaque aluminum bags with the same labeling form as real YMJ.

#### Distribution and administration

An independent pharmacist will distribute the experimental agent packages to the subjects in a separate room and the CRC will check to ensure that the distribution is correct. The subjects will be instructed to dissolve the YMJ or placebo granules from each package in water and take them 2 h after each meal. Voucher specimens of YMJ will be retained at the research laboratory of the manufacturer.

The investigator will monitor compliance with the study treatments by carrying out a telephone conference once a week between on-site visits. During the telephone conference, the investigator will inquire how many study agents the pharmacist has administered and will record the number on a case report form (CRF). If a subject does not take all of the YMJ or placebo, they will be asked to return the unused portion to the CRC at the next visit. The CRC and clinical pharmacist will double-check and document the amount of the returned portions. Finally, clinical research associates (CRAs) will check compliance with the study agents at the end of the study.

YMJ and its placebo will be kept and managed by clinical pharmacists who are independent of the investigators. The clinical pharmacists will record the date and the number of study agents during distribution and return.

### Outcome measurement

#### Primary outcome

VAS for xerostomia was chosen as a primary outcome to evaluate the subject’s improvement regarding discomfort due to xerostomia (ranging from 0 mm as no xerostomia to 100 mm as the most severe xerostomia). The measurements of VAS will be carried out at screening, baseline, at 4 weeks, and 8 weeks during YMJ administration, and at the end of study (10 weeks after baseline). The change of VAS scores before and after intervention (from week 0 to week 8) will be compared between the YMJ and placebo groups.

#### Secondary outcomes

##### Dry mouth symptom questionnaire

The dry mouth symptom questionnaire (DMSQ)
[27] is composed of six questions to evaluate subjective oral dryness by using the VAS and four questions to evaluate behavior to avoid oral dryness (using the Likert scale). The measurements will be carried out at baseline and at 4 weeks, 8 weeks, and 10 weeks.

##### Unstimulated and stimulated salivary flow rate

The unstimulated (USFR) and stimulated salivary flow rate (SSFR) are secondary outcomes that will be used to evaluate the effects of YMJ. The overall salivary flow rate will be determined by the draining method
[28]. Briefly, the subjects will be asked to rest for 10 min before clearing the mouth by swallowing all saliva within the oral cavity. Then, they will be instructed to place their tongue above a graduated cylinder (marked to the nearest 0.1 mL) for 10 min, and the drooled saliva will be collected. After 10 min of collection, the volume of the collected saliva will be measured. According to the criteria proposed by Ericsson and Hardwick
[29], hyposalivation will be defined as an USFR <0.1 mL/min.

Next, the subjects will be asked to chew a paraffin film (Parafilm: Pechiney Plastic Packaging Company, Chicago, IL, USA) and the saliva that is induced by chewing will be collected in a graduated cylinder. After 5 min, the volume of the saliva will be measured. These measurements will be carried out at screening, baseline, 4 weeks, 8weeks, and 10 weeks.

##### Residual saliva

The volume of residual saliva in the subject’s mouth will be measured to examine the effect of YMJ on the change in intra-oral saliva. The investigator will check the volume of residual saliva on the subject’s tongue and bucca by using the Moisture Checker for Mucus (MCM: Life Co, Ltd, Tokyo, Japan). This measurement will be carried out at baseline, 4 weeks, 8 weeks, and 10 weeks.

##### Salivary immunoglobulin A, salivary chromogranin A, and salivary cortisol

Salivary immunoglobulin (Ig) A, chromogranin A, and cortisol are well-established biologic markers of stress in the human body and are associated with salivary gland secretion
[30-34]. These measurements will be carried out at baseline and at 8 weeks.

In our study, the saliva sample will be collected between 09:00 and 10:00, and the salivary cortisol concentration will be determined by using the ER HS SALIVARY CORTISOL kit (Salimetrics, State College, PA, USA). The salivary Ig A will be examined by using the Salivary Secretory Ig A indirect enzyme Immunoassay Kit (Salimetrics, State College, PA, USA). Salivary chromogranin A will be assessed by using the Chromogranin A (Human) EIA Kit (Yanaihara, Japan). The analysis will be conducted by using a microplate reader (Molecular Devices, Sunnyvale, CA, USA), according to the manufacturer’s instructions.

##### ‘Yin-deficiency’ Questionnaire 1

The development and validation of the ‘*Yin-deficiency*’ questionnaire 1 (Yin-DQ1) was described in a previous study
[14]. This questionnaire consists of 10 VAS-related items: an irritable rash on the palms or soles, flushing of the zygomatic area in the afternoon, tidal fever, night sweats, emaciation or weight loss, dry mouth and/or throat, dizziness, constipation, decreased urine with yellowish color, and insomnia. The subjects will take this questionnaire at baseline and 8 weeks.

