## Methods/Design

### Objectives

The aims of this study are to:

(1) obtain clinical evidence regarding the safety and effects of YMJ in elderly individuals with xerostomia;

(2) identify a correlation between xerostomia in the elderly and the ‘*Yin-deficiency*’ state.

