#### Statistical analysis

An independent statistician will perform a blind statistical analysis using SPSS 16.0 (SPSS Inc., Chicago, IL, USA). All data will be presented as means and SDs, and all analyses will be based on the intention-to-treat principle.

The analysis strategies in the present study are as follows.

First, we will use the ANCOVA to compare the changes in VAS scores (primary outcome) to evaluate the effects of YMJ and the placebo from the beginning (0 week) to the end (8 weeks) of the study period. Second, the secondary outcomes (DMSQ scores, USFR, SSFR, volume of residual saliva, salivary Ig A, chromogranin A, cortisol, and ‘*Yin-deficiency*’ score) will be analyzed in the same manner as the primary outcome. Finally, correlation between subjective (VAS and DMSQ) and objective xerostomia-related variables (USFR, SSFR, and residual saliva) will be analyzed by Pearson’s correlation coefficients. Also, we will find out how xerostomia-related variables correlate with ‘*Yin-deficiency*’ score or stress-related variables (salivary Ig A, chromogranin A, and cortisol), respectively, using Pearson’s correlation coefficients. In addition, we will check the AEs in YMJ and placebo group each and describe them using the descriptive statistics.

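### The Yin-deficiency score contains a dry-mouth item, so its planned correlations with the xerostomia VAS and the DMSQ are inflated by overlap; a nine-item score would remove this

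*Protocol article*

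**What the plan says.** The Objectives section gives as its second aim to "identify a correlation between xerostomia in the elderly and the" Yin-deficiency state.

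The section on 'Yin-deficiency' Questionnaire 1, under Secondary outcomes, describes the instrument: "This questionnaire consists of 10 VAS-related items". The item list includes "emaciation or weight loss, dry mouth and/or throat, dizziness, constipation". The questionnaire is completed at baseline and at 8 weeks, and its development and validation are referred to an earlier study.

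The Statistical analysis section defines the variables to be used as "subjective (VAS and DMSQ) and objective xerostomia-related variables (USFR, SSFR, and residual saliva". It then states that "we will find out how xerostomia-related variables correlate with" the Yin-deficiency score, "using Pearson’s correlation coefficients".

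The Primary outcome section describes the xerostomia VAS as "ranging from 0 mm as no xerostomia to 100 mm as the most severe xerostomia". The DMSQ section says that six of its ten questions are VAS ratings of oral dryness. No section removes the dry-mouth item from the Yin-DQ1 or plans a score without it.

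Two further statements bear on weight. The Sample size calculation section treats the correlation as a pilot assessment in 96 subjects, to be shown descriptively. The Discussion says that a high correlation would be reasonable evidence for prescribing YMJ in this population.

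**The concern.** The question behind the second aim is whether the Yin-deficiency pattern accompanies dry mouth. A score that already counts dry mouth as one of its ten components cannot answer that independently: the same subject rates the same symptom in the same format on both sides of the coefficient. Even if the nine other features (night sweats, insomnia, constipation and so on) had nothing to do with dry mouth, the expected correlation with the VAS and the DMSQ would be above zero.

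At stake is the reading of the second aim. The abstract says the correlation will clarify whether Yin-deficiency is the main cause of xerostomia in the elderly, and the Discussion links it to prescribing. The primary efficacy comparison is not affected.

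**Working it through.** **Inputs from the article.** Ten VAS items, one of them dry mouth/throat ('Yin-deficiency' Questionnaire 1); Pearson's r against VAS, DMSQ, USFR, SSFR and residual saliva (Statistical analysis); n = 96 (Sample size calculation). The article states no expected correlation, power or precision for this analysis, so there is no figure to reproduce.

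**Assumptions, since the article gives no values.** The score is the sum (or mean) of ten items with equal variance. The dry-mouth item correlates r with the xerostomia VAS. The nine other items are unrelated to dry mouth and have mean correlation ρ among themselves.

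**Overlap alone.** The covariance of the VAS with the total comes only from the dry-mouth item. The variance of the total is 10 + 9 × 8 × ρ, so

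built-in r = r / √(10 + 72ρ).

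| Item–VAS correlation r | ρ = 0 | ρ = 0.1 | ρ = 0.2 | ρ = 0.3 |
|---|---|---|---|---|
| 0.5 | 0.16 | 0.12 | 0.10 | 0.09 |
| 0.6 | 0.19 | 0.15 | 0.12 | 0.11 |
| 0.8 | 0.25 | 0.19 | 0.16 | 0.14 |
| 1.0 | 0.32 | 0.24 | 0.20 | 0.18 |

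For example, 0.5/√10 = 0.16, 1.0/√10 = 0.32 and 0.5/√31.6 = 0.09. The same formula serves for the DMSQ, with the item–DMSQ correlation as r.

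**Against a significance yardstick.** The two-sided 5% critical value is t/√(n − 2 + t²) = 0.201 at n = 96. By Fisher's z, overlap alone passes it in about 46% (r = 0.6) to 70% (r = 0.8) of trials at ρ = 0; a simulation of 4,000 runs gave 47% and 70%. At ρ = 0.3 the figures are 18% and 28%. The nominal rate is 5%.

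**Sensitivity to equal variances.** If the dry-mouth item has q times the SD of the others and ρ = 0, the built-in value is rq/√(q² + 9). For r from 0.6 to 1.0 this gives 0.10 to 0.16 at q = 0.5 and 0.33 to 0.56 at q = 2.

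**Salivary measures.** These share no item with the Yin-DQ1. If the dry-mouth item correlates −0.2 to −0.4 with flow rate, the indirect contribution is −0.2/√10 = −0.06 to −0.4/√10 = −0.13.

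**Effect of leaving the item out.** With no true relation, the nine-item score gives an expected r of 0. Suppose there is a relation: each other item correlates 0.2 with the VAS, all items intercorrelate at 0.2, and the dry-mouth item correlates 0.7 with the VAS. The ten-item score then gives (0.7 + 9 × 0.2)/√(10 + 90 × 0.2) = 2.5/√28 = 0.47, and the nine-item score gives 1.8/√(9 + 72 × 0.2) = 1.8/√23.4 = 0.37. A true association therefore survives the change.

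**The case against.** The case for leaving the plan alone has real content. The aim is labelled pilot and descriptive, no significance criterion is set for it, and the prescribing inference is conditional on a high correlation. Dry mouth is a recognised feature of Yin-deficiency in the article's own account, and the ten-item form is the one cited as validated. The salivary measures, which share no item with it, are correlated with the score as well.

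This limits the weight of the point but does not remove it. A descriptive coefficient is inflated just as a tested one is. That dry mouth belongs to the pattern is a reason to use the item when identifying the pattern, not when asking whether the pattern goes with dry mouth. Nor is this a detail left to an analysis plan that is not shown: the article already fixes the instrument, its items, the variables and the method.

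Three stronger readings are tempting and are not supported.

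- A reader might infer that the trial would report an association even with nothing behind it. Several of the values above lie below 0.201, and the entry threshold on the xerostomia VAS may narrow its range and lower them further. It could happen; it need not.
- A reader might infer that all the planned correlations are affected alike. The direct overlap is confined to the VAS and the DMSQ.
- A reader might infer that the treatment comparison on the Yin-DQ1 is biased. That comparison is randomized, and the shared item does not bias the difference between groups. A score that falls when dry mouth improves is behaving as designed, though which items moved is a fair question of interpretation.

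**Conclusion.** The point holds for the correlations of the Yin-deficiency score with the xerostomia VAS and the DMSQ. With equal item variances and nine other items unrelated to dry mouth and to each other, overlap alone contributes about 0.16 to 0.32; it is lower, down to about 0.09, if those items intercorrelate at up to 0.3. This is enough to mislead about a weak or moderate association. With equal item variances it is not enough to produce a high one. The size rests on an assumed scoring rule and assumed item correlations; the direction follows from the item list itself, provided the dry-mouth item correlates positively with the VAS and the DMSQ. It is a modest, cheaply corrected weakness in a pilot aim.

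**What to change.** Add a sentence to the analysis plan: for the correlations of Yin-deficiency with the VAS and the DMSQ, the conclusion for the second aim rests on the Yin-DQ1 score without the dry mouth/throat item (nine items), and the ten-item score is reported beside it. State the scoring rule at the same place.

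For the treatment comparison keep the ten-item score; a nine-item result there is optional and serves interpretation only.

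The cost is one or two sentences, with no added data or visits, since the items are recorded anyway. The downside is that the nine-item version is not the one that was validated, which is why both should be shown.

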#### Safety

We will perform the following tests on all subjects at screening and after completion of YMJ administration: complete blood cell count; levels of aspartate aminotransferase/alanine aminotransferase, gamma-glutamyltranspeptidase, blood urea nitrogen, and creatinine; and erythrocyte sedimentation rate. These blood tests will help us to exclude subjects who have serious diseases and abnormal liver, heart, kidney, or other organ function. Throughout the present study, we will also check whether the 8-week administration of YMJ in xerostomia patients is safe by using these tests or CRF documentations.

In addition, at each visit, investigators will ask the subjects whether there are any adverse events (AEs) during the study period. If there is any AE, the investigator will provide the appropriate treatment to the subject immediately and record AEs in the dedicated document of the CRF including its severity and causality with the experimental agent. These AEs occurred during the entire study will be reviewed and monitored by independent CRA.

In the case of serious adverse events (SAEs), the investigator will offer the corresponding treatment to the subject immediately and report to IRB within 24 h from the time of recognition. If necessary, blind will be broken by adequate procedure and the documented procedure will be kept in the investigator study file.

#### Quality control

To retain the accuracy and quality of the clinical trial, DreamCIS, an established CRO located in Seoul, Korea, will audit the study. In addition, regular monitoring will be implemented by the CRA to ensure that the clinical trial is proceeding according to the protocol by checking trial master files, informed consent forms, the CRF, adverse events, and compliance with study agents.

#### Statistical analysis

An independent statistician will perform a blind statistical analysis using SPSS 16.0 (SPSS Inc., Chicago, IL, USA). All data will be presented as means and SDs, and all analyses will be based on the intention-to-treat principle.

The analysis strategies in the present study are as follows.

First, we will use the ANCOVA to compare the changes in VAS scores (primary outcome) to evaluate the effects of YMJ and the placebo from the beginning (0 week) to the end (8 weeks) of the study period. Second, the secondary outcomes (DMSQ scores, USFR, SSFR, volume of residual saliva, salivary Ig A, chromogranin A, cortisol, and ‘*Yin-deficiency*’ score) will be analyzed in the same manner as the primary outcome. Finally, correlation between subjective (VAS and DMSQ) and objective xerostomia-related variables (USFR, SSFR, and residual saliva) will be analyzed by Pearson’s correlation coefficients. Also, we will find out how xerostomia-related variables correlate with ‘*Yin-deficiency*’ score or stress-related variables (salivary Ig A, chromogranin A, and cortisol), respectively, using Pearson’s correlation coefficients. In addition, we will check the AEs in YMJ and placebo group each and describe them using the descriptive statistics.

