## Background

Xerostomia, which is a subjective sense of oral dryness
[1], is a fairly common condition among the elderly
[2]. It is estimated that approximately 30% of the population aged 65 years and older have xerostomia
[3], and several studies have reported a higher prevalence in the elderly than in the younger population
[4-7].

The causes of xerostomia are long-term uses of xerostomia-inducing medications for chronic diseases and systemic diseases (for example, Sjögren’s syndrome, diabetes mellitus, Alzheimer’s disease, and Parkinson’s disease), head and neck radiation therapy, aging, heavy smoking, and stress
[8]. In the elderly, the long-term use of medications and aging are regarded as major causes of xerostomia
[9]. However, recent xerostomia studies mostly focused on Sjögren’s syndrome or postradiotherapy-induced xerostomia, which are related to salivary gland damage, and only a few studies have assessed xerostomia in elderly subjects who did not exhibit obvious structural damage of the salivary glands
[10,11].

Xerostomia is not generally accepted as a disease despite its high prevalence in the elderly; therefore, this condition continues to impair the affected patient’s quality of life (QoL)
[7,12]. For example, xerostomia in the elderly is known to cause dental problems and changes in chewing, swallowing, digestion, and taste
[12]. Therefore, many xerostomia patients turn to solutions such as frequent water intake, sour foods, and alternative therapies (herbs or nutritional supplements)
[13]. However, it is unclear whether these behaviors or therapies provide relief from xerostomia symptoms.

In traditional Korean medicine (TKM), ‘*Yin-Deficiency*’ is regarded as the main pathologic cause of xerostomia in the elderly
[14]. Generally, the balance of *Yin* and *Yang* is important for maintaining health and treating diseases in TKM
[14]. Particularly, *Yin* in ‘*Yin-Deficiency*’ refers to general body fluids, including blood, and *Jing* (mostly translated as ‘essence of body’)
[15]. Therefore, ‘*Yin-Deficiency*’ is closely correlated with a shortage of body fluids, which results in various symptoms (dry mouth, dry eyes, or constipation)
[14]. TKM has many herbal prescriptions for treating ‘*Yin-Deficiency*’
[10,16].

*Yukmijihwang-tang* (YMJ; *Liu-wei-di-huang-tang* in traditional Chinese medicine; *Lokumijio-to* in Kampo Medicine) is described in the ancient Chinese literature, ‘*Key to Therapeutics of Children’s Diseases*’

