### Design

This is an academic research study that will be conducted as a randomized, placebo-controlled, double-blind, two-center trial at Kyung Hee University Korean Medicine Hospital and Kyung Hee University Hospital at Gangdong in Seoul, Korea.

This clinical trial will consist of an 8-week oral administration of YMJ with two visits at 4-week intervals and a 2-week follow-up period. Before enrollment, all subjects will go through a 7-day run-in period.

After randomization, all subjects will be divided into two groups: the YMJ and placebo groups. Each group will be provided with YMJ or a placebo for 8 weeks and the subjects will be required to take 3 g of YMJ or placebo three times a day. During the 8-week administration period, subjects will be prohibited from taking any kind of xerostomia-relieving drug such as pilocarpine or cevimeline. Primary and secondary outcomes will be measured at baseline and at 4 weeks, 8 weeks, and 10 weeks after randomization.

The flow of the entire trial is shown in Figure 
1.

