### Inclusion and exclusion criteria

In general, the definition of elderly is used to describe people over the age of 60 years
[24]; in accordance, we will recruit subjects who are between 60 and 80 years of age and have experienced xerostomia for 3 months prior to participation. We have restricted the subjects’ ages to below 80 years because individuals over this age are considered to have lower eligibility in this study on the basis of the rationale that the incidence of disease is increased as an individual ages.Therefore, we set an upper limit of 80 years on the subjects’ ages by a consensus among geriatric disease specialists.

The subjects should present with VAS scores >4 for xerostomia 2 weeks before the study period. In addition, the unstimulated salivary flow rates of the subjects should be under 0.3 mL/min. The subjects must agree that they will not receive xerostomia-related treatments for 3 months after initiation of the study.

Subjects who report the following conditions will be excluded:

(1) a history of treatments for autoimmune diseases like Sjögren’s syndrome, rheumatism, or lupus;

(2) a history of craniocervical radiation therapy, organ transplantation, severe psychiatric illness, or major depression;

(3) the use of any other herbal prescriptions or nutritional supplements at the screening phase;

(4) the use of xerostomia-relieving medications (pilocarpine and cevimeline) or therapies for xerostomia (mouthwash, gum, and toothpaste for xerostomia).

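### The Yin-deficiency correlation is planned as an unadjusted Pearson coefficient, although the protocol itself names medication and aging as major causes of dry mouth in the elderly

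*Protocol article*

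**What the plan says.** All places are in the protocol article.

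- **Causes.** The Background gives a general list: "The causes of xerostomia are long-term uses of xerostomia-inducing medications for chronic diseases and systemic diseases", followed by radiation, aging, smoking and stress. For the target population it is more specific: "In the elderly, the long-term use of medications and aging are regarded as major causes of xerostomia".
- **What is controlled.** Inclusion and exclusion criteria rule out "the use of xerostomia-relieving medications (pilocarpine and cevimeline) or therapies for xerostomia" and also "the use of any other herbal prescriptions or nutritional supplements at the screening phase". They further exclude treated autoimmune disease, craniocervical radiation and some other histories. Under Design, during the 8 weeks, "subjects will be prohibited from taking any kind of xerostomia-relieving drug such as pilocarpine or cevimeline". No section restricts, stratifies by or adjusts for medication that induces dry mouth. Age is bounded but free within the bounds: "we will recruit subjects who are between 60 and 80 years of age".
- **Analysis.** Under Statistical analysis, "we will find out how xerostomia-related variables correlate with" the Yin-deficiency score or the stress markers, by Pearson coefficients. ANCOVA is named only for the treatment comparisons.
- **Purpose.** Objectives, item 2, asks only for a correlation. Sample size calculation calls this aim a pilot with descriptive results. The Abstract goes further and says that the correlation will help settle whether Yin-deficiency is the main cause. The Discussion says that a high correlation would support prescribing YMJ.

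**The concern.** A two-variable coefficient cannot separate a proposed cause from causes that are already accepted and left free to vary. If older subjects, or those on drying drugs, have both more dry mouth and higher Yin-deficiency scores, the two scores will correlate even with no other link between them. This is plausible. The Yin-deficiency questionnaire asks about constipation, dizziness, reduced urine and insomnia, which age or medication could also influence. The documents do not quantify any such influence.

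What is at stake is the interpretation of objective 2. A coefficient that partly reflects age and medication could be presented as support for a causal theory and for using the study product.

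**Working it through.** **The plan's own figure.** None is given for the correlation. The total of 96 is taken over from the VAS comparison: 2 × 36 = 72, and 72 / 0.75 = 96. Whether 36 per group follows from the stated inputs is a separate question, and nothing below depends on it. The two sample sizes used here are 96 (all randomized) and 96 × 0.75 = 72 (after the assumed 25% dropout).

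**Critical values.** With r = t / √(n − 2 + t²) and t the two-sided 5% point on n − 2 degrees of freedom, significance needs |r| of 0.2006 at n = 96 and 0.232 at n = 72.

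**One binary common cause.** Assume that a share p of subjects take drying medication, that use shifts both the xerostomia score and the Yin-deficiency score by d within-group SDs, and that nothing else links the scores. The covariance is p(1 − p)d² and each variance is 1 + p(1 − p)d², so

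r = p(1 − p)d² / (1 + p(1 − p)d²).

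| p | d = 0.5 | d = 0.8 | d = 1.0 |
|---|---|---|---|
| 0.5 | 0.0625/1.0625 = 0.059 | 0.16/1.16 = 0.138 | 0.25/1.25 = 0.200 |
| 0.3 | 0.0525/1.0525 = 0.050 | 0.1344/1.1344 = 0.118 | 0.21/1.21 = 0.174 |

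The documents give neither p nor d, so both are assumptions. The top of this range, 0.200, lies just under the critical value.

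**A stronger common cause.** If a common cause correlates a with each score and the adjusted correlation is zero, the unadjusted r is a². The chance that it is significant, by Fisher's z, is:

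| a | r = a² | n = 96 | n = 72 |
|---|---|---|---|
| 0.3 | 0.09 | 0.14 | 0.12 |
| 0.4 | 0.16 | 0.34 | 0.27 |
| 0.5 | 0.25 | 0.69 | 0.56 |
| 0.6 | 0.36 | 0.95 | 0.88 |

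For a single binary drug factor at p = 0.5, r = 0.25 requires 0.25d² = 0.25/0.75, so d is about 1.15. Likewise r = 0.36 requires 0.25d² = 0.36/0.64, so d = 1.5. Both exceed the range in the first table.

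**Two independent common causes**, such as age and medication, add. With a = 0.3 for each, r = 2 × 0.09 = 0.18; with a = 0.4 for each, r = 2 × 0.16 = 0.32. At n = 96 these are significant with probability 0.42 and 0.89.

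**Cost of adjusting.** A partial correlation given two covariates has 96 − 4 = 92 degrees of freedom, with t = 1.986. The critical value is 1.986 / √(92 + 3.94) = 0.203, against 0.201 unadjusted.

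**The case against.** The best reply is that the protocol asks only for a correlation, calls it a pilot aim and promises descriptive results; for that, a Pearson coefficient is legitimate. As far as Objectives and Sample size calculation go, this is right. It does not cover the Abstract and Discussion, which draw a causal and a prescribing inference from the same coefficient.

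A second reply is that the effect may be modest. This stands in part. One drug factor in the assumed range does not reach significance in expectation, and the Discussion bases its inference on a high correlation. Values of 0.25 or more need stronger or combined causes.

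A third is that adjustment will not make the coefficient clean, because one of the ten questionnaire items asks about dryness of the mouth or throat and so shares content with the xerostomia VAS. This is correct and limits what the remedy can claim.

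A reader might also infer more than the documents support:

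- **That the YMJ–placebo comparison is biased.** It is randomized, and stable medication use does not bias it. Further covariates in the ANCOVA would be a matter of precision, and the covariate list may sit in the analysis plan.
- **That drug changes during the trial cannot be identified.** The article condenses a fuller protocol and refers to a case report form that is not shown; concomitant medication may well be recorded there.
- **That only relieving drugs are controlled.** Herbal prescriptions, supplements and several conditions are excluded too. The gap concerns drying medication.

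**Conclusion.** The point holds for objective 2. The stated method does not fit the inference that the Abstract and Discussion attach to it, because two causes that the protocol calls major are left to vary and are not taken into account. Open to confounding is the right strength: the documents do not show that the correlation will be spurious, nor by how much. Under the assumptions above, the induced r is about 0.05 to 0.20 for one binary drug factor, and 0.25 to 0.36 only if a common cause correlates 0.5 to 0.6 with both scores. It also has to be assumed that age and medication relate to the Yin-deficiency score, which is plausible from its items but not documented. This is an inexpensive improvement to a secondary aim and does not affect the primary result.

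**What to change.** - **Statistical analysis:** beside each unadjusted Pearson coefficient between a xerostomia variable and the Yin-deficiency score, report the partial correlation given age and baseline xerostomia-inducing medication (yes/no). Agree the drug list before unblinding.
- **Abstract and Discussion:** state the result as an association, not as evidence of cause or as grounds for prescribing. Mention the shared dry-mouth item as a limitation that adjustment does not remove.

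The cost is one coded baseline variable, agreement on a drug list and two degrees of freedom. Age is known from eligibility, and exclusions (3) and (4) already require questions about products in use at screening. No change to eligibility, treatment or visits is involved.
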